### 7.2 Outcome Definitions

The primary outcomes for this study are:

1. COVID-19 diagnosis will be defined as a SARS-CoV-2 positive molecular test or a COVID-19 diagnosis code (Primary Objective 1, Secondary Objectives 1-12, 14)
2. Severe COVID-19 disease includes COVID-19 hospitalization (hospitalization with a SARS-CoV-2 positive test or a COVID-19 diagnosis, or a hospitalization occurring  $\leq 7$  days after a SARS-CoV-2 positive test, with chart review to confirm severe COVID-19 symptoms) and COVID-19 mortality (death during COVID-19 hospitalization) (Primary Objective 2, Secondary Objectives 13, 15)

We will ascertain the first occurrence of COVID-19 diagnosis or severe COVID-19 disease  $\geq 14$  days after the index date.

Incident COVID-19 cases (identified through diagnosis code or positive molecular test) will be separated into symptomatic and asymptomatic COVID-19 cases. COVID-19 symptoms will be identified using a natural language processing (NLP) algorithm (currently being submitted for publication). The NLP algorithm will be applied to clinical notes before and after the incident COVID-19 diagnosis date to search for COVID-19 related symptoms. COVID-19 cases with no symptoms identified will be considered asymptomatic cases.

Positive SARS-CoV-2 tests conducted for surveillance of asymptomatic individuals will also be used as a preliminary approach to identify asymptomatic COVID-19 cases until the NLP algorithm is finalized. The use of testing data in asymptomatic individuals will facilitate assessment of VE against asymptomatic COVID-19 for the first interim analysis, whereas the

more comprehensive NLP approach will require more time to apply and will be used for subsequent analyses.

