## 1 Synopsis

Severe acute respiratory syndrome coronavirus 2 (SARS-CoV-2), the virus causing the coronavirus disease 2019 (COVID-19) pandemic, has caused high global morbidity and mortality,[1] with multiple SARS-CoV-2 variants of concern (VOCs) and variants of interest (VOIs) emerging over the course of the pandemic. [2-4] COVID-19 vaccines have been developed at unprecedented speed, including the Moderna mRNA-1273 SARS-CoV-2 vaccine (Moderna COVID-19 vaccine, hereafter), which received Emergency Use Authorization (EUA) in the United States (U.S.) on December 18, 2020.[5]

Moderna COVID-19 vaccine is a lipid nanoparticle encapsulated messenger RNA (mRNA)-based vaccine encoding the prefusion-stabilized spike glycoprotein of SARS-CoV-2. In a phase 3 randomized, observer-blinded, placebo-controlled trial enrolling approximately 30,000 participants, vaccine efficacy of Moderna COVID-19 vaccine was 94.1% and was generally consistent across age, sex, race/ethnicity, and risk status. No safety concerns were identified.[6] However, post-authorization studies are critically needed to determine Moderna COVID-19 vaccine effectiveness and durability in real-world settings among diverse populations.

In this protocol, we describe an observational cohort study at Kaiser Permanente Southern California (KPSC), a large, integrated health care system. The primary objectives are to evaluate the vaccine effectiveness (VE) of 2 doses of Moderna COVID-19 vaccine in preventing COVID-19 diagnosis and severe COVID-19 disease. COVID-19 diagnosis will be defined as a positive SARS-CoV-2 molecular diagnostic test among symptomatic or asymptomatic individuals or a diagnosis code. Severe COVID-19 disease will be defined as COVID-19 hospitalization or mortality. KPSC members meeting inclusion criteria will be considered exposed if they received 2 doses of Moderna COVID-19 vaccine during 2021, and the unexposed comparison group will be a similar unvaccinated population. Individuals will be followed through electronic health records for COVID-19 outcomes through December 2023, with 6 interim analyses and a final analysis being conducted.

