**Laboratory:** Includes laboratory orders and results.

**Pharmacy:** Includes National Drug Codes (NDC) and Generic Product Identifier (GPI) codes. More than 95 percent of members have a drug benefit with minimal copayments.

**Mortality:** Includes deaths from hospital and membership databases, as well as from state and national death files.

**Birth:** Includes pregnancy related information such as gestational age, birth weight, and Apgar scores.

**Clinical notes:** Allows for natural language processing of clinical notes to identify outcomes not easily identified through structured data.

Table 1. Demographic characteristics of Kaiser Permanente Southern California members on January 1, 2021

|                                            | Number of members |
|--------------------------------------------|-------------------|
| Total population                           | 4,573,594         |
| Sex                                 |                   |
| Male                                       | 2,360,957         |
| Female                                     | 2,212,637         |
| Age (years)                         |                   |
| <6                                         | 278,559           |
| 6 to <12                                   | 308,704           |
| 12 to <18                                  | 341,464           |
| 18 to <65                                  | 2,942,731         |
| 65 to <75                                  | 432,045           |
| ≥75                                        | 270,091           |
| Race                                |                   |
| White                                      | 2,470,912         |
| Black or African American                  | 359,270           |
| American Indian & Alaska Native            | 21,137            |
| Asian                                      | 487,947           |
| Native Hawaiian and Other Pacific Islander | 37,107            |
| Other race                                 | 1,172,221         |
| Two or more races                          | 25,000            |
| Ethnicity                           |                   |
| Hispanic or Latinx (of any race)           | 1,829,983         |

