| Number of patients tested for SARS-CoV-2 with RT-PCR test                       | 48,290      | 825,670 | 184,197 | 1,058,157 |
| Number of patients with a positive SARS-CoV-2 RT-PCR test                       | 13,788      | 200,403 | 24,452  | 238,643   |
| Number of patients with a COVID-19 diagnosis                        | 15,807      | 247,628 | 31,960  | 295,395   |
| Number of patients admitted to hospital with a COVID-19 diagnosis   | 87          | 10,871  | 7,980   | 18,938    |
| Number of patients admitted to ICU with a COVID-19 diagnosis        | 13          | 2,928   | 2,227   | 5,168     |
| Number of deaths within 31 days after the first COVID-19 diagnosis  | 1           | 715     | 2,038   | 2,754     |

A COVID-19 diagnosis includes those with a positive SARS-CoV-2 RT-PCR test result or a COVID-19 diagnosis code only.

As of December 31, 2020, over 1 million SARS-CoV-2 RT-PCR tests had been performed at KPSC, of which 17.4% were among individuals aged ≥65 years and 4.6% were among adolescents aged 12-17 years (Table 2). There were 238,643 members testing positive (13,788 members aged 12-17 years and 24,452 members aged ≥65 years). Additional members were diagnosed with COVID-19 based on positive test results outside of KPSC or clinical presentation and contact history, for a total of 56,752 members with a COVID-19 clinical diagnosis only. Approximately 25.0% (7,980/31,960) of COVID-19 patients aged ≥65 years were hospitalized, compared to only 4.4% (10,871/247,628) who were hospitalized among patients aged 18-64 years and 0.6% (87/15,807) who were hospitalized among patients aged 12-17 years. The proportion of COVID-19 patients being admitted to the ICU was 7.0% in patients aged ≥65 years versus 1.2% in patients aged 18-64 years. The proportion of COVID-19 patients who died within 31 days after a COVID-19 diagnosis or a positive test was 6.4% in patients aged ≥65 years versus 0.29% in patients aged 18-64 years.

As of July 2021, asymptomatic individuals who receive a COVID-19 test at KPSC may include individuals without COVID-19 symptoms who require or request testing. Both vaccinated and unvaccinated individuals are required to be tested for SARS-CoV-2 prior to KPSC procedures or admission. In addition, asymptomatic individuals can request testing (regardless of vaccination status) for any of the following reasons: travel, exposure to or close contact with a COVID-19-

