## 5 Study Design Overview

We will conduct an observational cohort study to evaluate the VE of Moderna COVID-19 vaccine in preventing COVID-19 diagnosis and severe COVID-19. Vaccine exposure, COVID-19 outcomes, and covariates will be identified from EHR, as described in Section 7 below. All individuals who receive Moderna COVID-19 vaccine from December 2020 to December 2021 and meet eligibility criteria specified in Section 6.1 below will be included in the study (“vaccinated”, hereafter). The unvaccinated comparator cohort will comprise individuals who have not received Moderna COVID-19 vaccine or any other COVID-19 vaccine as of the index date of their matched vaccinated individual (see Section 6.2 for details on index date) and who meet eligibility criteria specified in Section 6.1 below. Unvaccinated individuals who subsequently receive Moderna COVID-19 vaccine may contribute person-time to both unvaccinated and vaccinated cohorts. Individuals will be followed up through EHR for occurrence of COVID-19 outcomes until the end of the study period (December 31, 2023 for final analysis), or censoring events (termination of KPSC membership allowing for a 31-day gap, death, receipt of a COVID-19 vaccine).

Six interim analyses and a final analysis will be conducted. For the first and second interim analyses, unvaccinated individuals will be randomly selected and n:1 matched to vaccinated individuals by age, sex, and race/ethnicity (if sample size allows), and will be assigned an index date based on the vaccination date of their matched vaccinated individual. For subsequent interim analyses and the final analysis, the number of eligible unvaccinated individuals in the KPSC population may be insufficient for individual matching; if so, frequency matching will be employed. In all analyses, efforts will be dedicated to identifying and adjusting for potential confounders. Cox proportional hazards regression will be used to estimate unadjusted and adjusted HRs. VE (%) will be estimated as  $(1 - \text{adjusted HR}) \times 100$ . Propensity score analyses with inverse probability of treatment weighting (IPTW) will be considered for final analyses.

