|                                                      | 30                                                              | 80                         | >.999 |
|                                                      | 30                                                              | 70                         | >.999 |

For the first interim analysis of Primary Objective 2, we estimate an incidence of 2 COVID-19 hospitalizations and 0.3 deaths per 1,000 unvaccinated adult KPSC members during an average 4-month follow-up period. We expect to have >99.9% power to detect a 70% VE against COVID-19 hospitalizations, with various sample sizes in the unvaccinated group (Table 5).

Table 5. Power calculations for 1st interim analysis of Primary Objective 2 for various sample sizes and vaccine effectiveness estimates

| Sample Size Ratio
(Vaccinated vs
Unvaccinated) | Incidence rate in
unvaccinated group
(cases/1000 persons) | VE (%)
(reduction rate) | Power |
|------------------------------------------------------|-----------------------------------------------------------------|----------------------------|-------|
| 1 vs 0.5                                             | 2                                                               | 90                         | >.999 |
|                                                      | 2                                                               | 80                         | >.999 |
|                                                      | 2                                                               | 70                         | >.999 |
| 1 vs 1                                               | 2                                                               | 90                         | >.999 |
|                                                      | 2                                                               | 80                         | >.999 |
|                                                      | 2                                                               | 70                         | >.999 |
| 1 vs 5                                               | 2                                                               | 90                         | >.999 |
|                                                      | 2                                                               | 80                         | >.999 |

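### As defined, the severe COVID-19 outcome is COVID-19 hospitalization: the mortality component adds no events, and COVID-19 deaths in members never hospitalized with it are censored.

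*Protocol*

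**What the plan says.** The synopsis (section 1) states: "Severe COVID-19 disease will be defined as COVID-19 hospitalization or mortality". Section 3 describes the outcome in the same broad way. Neither restricts mortality by place of death.

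Section 7.2 is the operative definition. It has a hospitalization component, confirmed by chart review, and a mortality component given as "COVID-19 mortality (death during COVID-19 hospitalization". The counting rule is: "We will ascertain the first occurrence of COVID-19 diagnosis or severe COVID-19 disease", at least 14 days after the index date. The definition serves Primary Objective 2 and Secondary Objectives 13 and 15.

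Section 5 ends follow-up at the close of the study or at "censoring events (termination of KPSC membership allowing for a 31-day gap, death, receipt of a COVID-19 vaccine". It makes no exception for a death from COVID-19.

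On data, section 4 says deaths come from hospital and membership databases "as well as from state and national death files". Table 2 (section 4.2) reports the "Number of deaths within 31 days after the first COVID-19 diagnosis", with no limit on place of death.

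For planning, section 9 says "we estimate an incidence of 2 COVID-19 hospitalizations and 0.3 deaths per 1,000 unvaccinated adult KPSC members" over an average of 4 months. Table 5 gives separate power for hospitalization and for death. It has no row for the two combined.

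**The concern.** A composite of hospitalization or death normally includes death so that the worst outcomes count even when the patient never reached hospital. Here the death component sits wholly inside the hospitalization component, so it cannot do that. A reader of the synopsis would take the result as effectiveness against hospitalization or death, when it is effectiveness against hospitalization.

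A COVID-19 death at home or in a care facility, with no COVID-19 admission, is handled as censoring. Section 4.1 places long-term care residents in the first vaccination phase, so such deaths are plausible in this population.

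The death rows of Table 5 may also describe a wider set of deaths than section 7.2 admits. If so, they overstate the power to say anything about mortality as defined.

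**Working it through.** **1. Does the mortality component add events?** Death during a COVID-19 hospitalization requires a COVID-19 hospitalization, and that hospitalization is itself a severe event that starts no later than the death. Under the first-occurrence rule the death adds nothing. Section 10.2 states the same nesting for the variant cohort. Per 80,000 unvaccinated members, 2 per 1,000 gives 160 hospitalizations and 0.3 per 1,000 gives 24 deaths. If all 24 deaths are in hospital, the composite remains 160.

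**2. Which deaths are missed?**
- Death during a COVID-19 hospitalization: already an event.
- Death after discharge from one: already an event.
- COVID-19 death with no COVID-19 hospitalization: meets neither component and is censored at death.

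Only the third group is lost. If the 0.3 covers all COVID-19 deaths, the loss is at most 0.3/2 = 15% of the hospitalization count. A composite counting every COVID-19 death would have 160 to 184 events per 80,000 (2.0 to 2.3 per 1,000). The protocol gives no figure for where in that range the truth lies.

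**3. Reproducing Table 5.** Inputs from section 9: 80,000 vaccinated, two-sided alpha 0.007 (z = 2.697), death risk p0 = 0.0003 in the unvaccinated and p1 = p0 × (1 − VE). The formula is the pooled normal approximation for two proportions:

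power = Φ{[(p0 − p1) − z·SE0] / SE1}

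SE0 uses the pooled proportion and SE1 the separate proportions. At 1 vs 1 and VE 80%, p0 − p1 = 0.00024 and SE0 ≈ SE1 ≈ 0.0000671, so power = Φ(3.578 − 2.697) = Φ(0.881) = 0.81, as stated.

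| Ratio | Table 5 (VE 90/80/70%) | Recomputed |
|---|---|---|
| 1 vs 0.5 | 0.84 / 0.69 / 0.51 | 0.842 / 0.688 / 0.505 |
| 1 vs 1 | 0.93 / 0.81 / 0.62 | 0.934 / 0.811 / 0.622 |
| 1 vs 5 | 0.99 / 0.97 / 0.82 | 0.999 / 0.968 / 0.822 |

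The arithmetic of Table 5 is sound. The open question is its input rate.

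**4. Where does 0.3 come from?** Adult counts in Table 2:
- diagnoses: 247,628 + 31,960 = 279,588
- hospitalizations: 10,871 + 7,980 = 18,851
- deaths within 31 days: 715 + 2,038 = 2,753

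Applied to the planned 30 diagnoses per 1,000:
- hospitalizations: 30 × 18,851/279,588 = 2.02 per 1,000 (stated 2)
- deaths: 30 × 2,753/279,588 = 0.295 per 1,000 (stated 0.3)

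Both planning rates come out of the same table, and its death count has no limit on place. That is a strong inference, but the protocol does not state the source.

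**5. Power of the death rows at a lower in-hospital rate** (1 vs 1, same formula; the shares are assumptions):

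| Share of deaths outside a COVID-19 hospitalization | Rate per 1,000 | Power at VE 90/80/70% |
|---|---|---|
| 0% | 0.3 | 0.93 / 0.81 / 0.62 |
| 25% | 0.225 | 0.83 / 0.66 / 0.46 |
| 37.5% | 0.1875 | 0.73 / 0.55 / 0.37 |
| 50% | 0.15 | 0.61 / 0.43 / 0.28 |

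**6. Effect on the composite.** At 2.0 or 2.3 per 1,000 and VE 70%, power exceeds 0.999 at every ratio. For the estimate, suppose VE is 90% against hospitalization and 70% against the missed deaths (both assumed). VE against any severe outcome is then 1 − (2 × 0.1 + m × 0.3)/(2 + m). This is 89.7% with m = 0.03 missed deaths per 1,000 and 87.4% with m = 0.3, against 90% as defined.

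**The case against.** The synopsis is a summary. Section 7.2 is the operative text, and sections 10.1 and 10.2 keep to the same idea of hospitalized death. A chart-confirmed, in-hospital definition can be a deliberate choice for specificity. This stands: the definition is usable and applied consistently. It does not remove the gap between label and content. The protocol gives no reason for the restriction, and section 13 does not list uncounted deaths as a limitation.

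A reader might infer three stronger points that the documents do not support.

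- *That all COVID-19 deaths outside hospital are treated as non-events.* Anyone who dies after discharge from a COVID-19 hospitalization already has the event. Only members never hospitalized with COVID-19 are lost, and those with a positive test or diagnosis code can still count under Primary Objective 1.
- *That Objective 2 can say nothing about mortality.* Table 5 treats death separately, and in-hospital death can be reported as its own component.
- *That the estimate is materially biased or underpowered.* If a similar share of events is missed in both groups, the hazard ratio hardly moves, and nothing in the protocol shows a differential loss. The weaker power concerns a death-only comparison at the first interim analysis, for which section 9 claims no adequacy. Accrual is expected to reach 500,000 to 1,000,000. At 500,000 per group, even 0.1875 per 1,000 and VE 70% gives power of 0.999.

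Making any death within 31 days part of the primary outcome is also open to challenge. Section 4.2 requires testing before procedures and admissions, so incidental positives followed by unrelated deaths would enter and could pull VE toward zero. For that reason the wider count belongs in a sensitivity analysis.

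**Conclusion.** The point holds as a mismatch between what Objective 2 is said to measure and what it measures. By the protocol's own wording, severe COVID-19 equals COVID-19 hospitalization, and COVID-19 deaths in members never hospitalized with the disease are censored. This part needs no assumption.

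The size is limited. Missed deaths are at most 15% of the hospitalization count, provided the 0.3 rate covers all COVID-19 deaths. Power for the composite is unaffected, and any shift in VE is probably small unless protection against never-hospitalized death differs greatly from protection against hospitalization.

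That the Table 5 death rows use deaths in any setting is inferred from matching figures. Table 2's count is wider than section 7.2 as to place, although its 31-day limit would leave out later in-hospital deaths. The power loss, such as 0.81 to 0.66 at 1 vs 1 and VE 80%, rests on an assumed 25% share outside a COVID-19 hospitalization. The death rows may be too high, but by how much cannot be settled from the protocol.

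**What to change.** 1. Describe the outcome of Primary Objective 2 and Secondary Objectives 13 and 15 consistently as COVID-19 hospitalization (including in-hospital death), in the synopsis, section 3 and section 7.2.
2. Add a pre-specified sensitivity analysis in which any death within 31 days after a positive molecular test or COVID-19 diagnosis, wherever it occurs, also counts as an event and is not censored. The 31-day window is the one Table 2 already uses, and the death files are already held.
3. State in section 9 which deaths the 0.3 per 1,000 covers. If the in-hospital definition stays, restate the Table 5 death rows at the in-hospital rate.

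The cost is wording, one linkage to existing death files and one rerun of the power calculation. The downside is that some deaths from other causes will enter the sensitivity analysis. Death files may also be incomplete at the early interim analyses: section 8.1 applies no data lag to the first three, and the protocol does not say how current the files are. Results from those analyses should carry that caveat.

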#### Exclusion criteria

- Receipt of a COVID-19 vaccine other than Moderna COVID-19 vaccine prior to or on the index date
- Receipt of 2 doses of Moderna COVID-19 vaccine  $< 24$  days apart [13] for 2-dose exposed cohort
- Receipt of any COVID-19 vaccine  $< 14$  days after the index date
- No health care utilization and no vaccination from the 2 years prior to the index date through the index date
- Occurrence of a COVID-19 outcome  $< 14$  days after the index date

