| Other variables                                                                                             |                                     |
| KPSC physician/employee status at index date                                                                       | Yes, No                             |
| Frailty index in year prior to index date (-365 to -1 day, inclusive), using method by Kim et al. [15]             | To be determined based on quartiles |
| History of COVID-19 diagnosis (from March 1, 2020 to index date, inclusive)                                        | Yes, No                             |
| History of SARS-CoV-2 molecular test performed (from March 1, 2020 to index date, inclusive), regardless of result | Yes, No                             |
| Concomitant vaccine                                                                                                | Yes, No                             |
| Immunocompromised status                                                                                    | Yes, No                             |
| HIV/AIDS any time prior to index date                                                                              | Yes, No                             |
| Leukemia, lymphoma, congenital immunodeficiencies, asplenia/hyposplenism any time prior to index date              | Yes, No                             |
| Organ transplant any time prior to index date                                                                      | Yes, No                             |
| Immunosuppressant medications at index date                                                                        | Yes, No                             |

\* Charlson comorbidities include myocardial infarction, congestive heart failure, peripheral vascular disease, cerebrovascular disease, connective tissue disease, dementia, chronic pulmonary disease, connective tissue disease, peptic ulcer disease, diabetes mellitus, paraplegia and hemiplegia, renal disease, liver disease, cancer, metastatic solid tumor, human immunodeficiency virus (HIV), and acquired immunodeficiency syndrome (AIDS)

The covariates included in adjusted analyses will be determined by scientific relevance, association with exposure, and data availability. Specifically, we will select covariates by following these steps:

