**Secondary Objective 6:** For Secondary Objective 6, analyses will include individuals who are frail, identified using the method by Kim et al.[15] We will calculate COVID-19 diagnosis incidence, unadjusted and adjusted HRs and VEs, as described for the primary analysis above.

**Secondary Objective 7:** For Secondary Objective 7, analyses will include pregnant women. We will calculate COVID-19 diagnosis incidence, unadjusted and adjusted HRs and VEs, as described for the primary analysis above.

**Secondary Objective 8:** For Secondary Objective 8, analyses will include individuals with a history of COVID-19 diagnosis. Incident COVID-19 diagnosis (a COVID-19 reinfection, >90 days after the most recent prior COVID-19 diagnosis code or SARS-CoV-2 positive molecular test) during follow-up will be assessed using two definitions. The first definition will require a COVID-19 diagnosis code with chart-confirmed symptoms or a SARS-CoV-2 positive molecular test. The second, more specific definition will require a COVID-19 diagnosis code with chart-confirmed symptoms, a SARS-CoV-2 positive molecular test with chart-confirmed symptoms, or a SARS-CoV-2 positive molecular test with an intervening SARS-CoV-2 negative molecular test. We will calculate COVID-19 diagnosis incidence, unadjusted and adjusted HRs and VEs, as described for the primary analysis above.

**Secondary Objective 9:** CDC initially recommended that COVID-19 vaccines be routinely administered alone, with a minimum interval of 14 days before or after administration with any other vaccine. In May 2021, CDC updated their recommendations to indicate that COVID-19 vaccines and other vaccines may be administered without regard to timing; this includes administration of COVID-19 vaccines and other vaccines on the same day as well as within 14 days of each other. For Secondary Objective 9, we will compare individuals who received either the first or second dose of Moderna COVID-19 vaccine concomitantly with another vaccine (i.e., on the same day) with unvaccinated individuals. We will calculate COVID-19 diagnosis incidence and unadjusted and adjusted HRs and VEs, as described for the primary analysis above.

**Secondary Objective 10:** For Secondary Objective 10, we will calculate VE of 2 doses of Moderna COVID-19 vaccine against asymptomatic COVID-19. We will calculate the incidence of asymptomatic COVID-19 and estimate unadjusted and adjusted HRs and VEs, as described for the primary analysis above.

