### 10.1 Test-negative design (TND)

#### Inclusion criteria

- Aged  $\geq 18$  years (aged  $\geq 12$  years once Moderna COVID-19 vaccine is authorized in this age group) as of date of specimen collection for the SARS-CoV-2 test (Day 0)
- KPSC member for  $\geq 12$  months prior to Day 0 (Day -365 to Day 0, inclusive, and allowing a 31-day gap)
- Tested positive for SARS-CoV-2 by PCR at KPSC with specimen collected on or after 3/1/2021 and sent for WGS, without a history of a COVID-19 diagnosis code or SARS-CoV-2 positive molecular test in the 90 days prior to the test; or tested negative for SARS-CoV-2 by PCR with specimen collected on or after 3/1/2021

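### The COVID-19 diagnosis outcome in Section 7.2 has no 90-day rule for earlier infection, so repeat codes and lingering positives can count as new events in Primary Objective 1, and the definition conflicts with Section 8.4

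*Protocol*

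**What the plan says.** Section 7.2 defines the first primary outcome and its scope in one sentence: "COVID-19 diagnosis will be defined as a SARS-CoV-2 positive molecular test or a COVID-19 diagnosis code (Primary Objective 1, Secondary Objectives 1-12, 14". The timing rule follows: "We will ascertain the first occurrence of COVID-19 diagnosis or severe COVID-19 disease", from day 14 after the index date. Neither sentence refers to infection before the index date.

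The only COVID-19 exclusion in Section 6.1 is "Occurrence of a COVID-19 outcome" fewer than 14 days after the index date. People with earlier COVID-19 stay in the cohort. Table 3 lists their history as a possible covariate, "History of COVID-19 diagnosis (from March 1, 2020 to index date, inclusive", coded Yes or No with no recency.

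Two other places do set an interval:
- Section 8.4, Secondary Objective 8, defines the incident event as "a COVID-19 reinfection, >90 days after the most recent prior COVID-19 diagnosis code or SARS-CoV-2 positive molecular test".
- Section 10.1 requires test-positive cases to be "without a history of a COVID-19 diagnosis code or SARS-CoV-2 positive molecular test in the 90 days prior to the test".

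The severe outcome in Section 7.2 has a different safeguard: hospitalizations are included "with chart review to confirm severe COVID-19 symptoms".

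**The concern.** Take a person diagnosed three weeks before the index date whose follow-up visit is coded on day 20. Under Section 7.2 that code is an event in Primary Objective 1. Under Section 8.4 the same code is not an event in Secondary Objective 8, because it falls 41 days after the diagnosis. Yet Section 7.2 names Objectives 1-12, and so Objective 8, as users of the definition without the rule. The two sections cannot both be followed.

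The setting gives such records several ways to arise. Section 4.2 describes required testing before procedures and admissions, and voluntary weekly testing of staff. Section 13 says positive tests from outside are documented with internal diagnosis codes. In Table 2, 56,752 of 295,395 diagnoses (19%) were clinical only.

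When true VE is high the vaccinated arm has few real cases, so a small number of carried-over records weighs heavily in its numerator. Adjusting for history compares like with like but leaves the false events in the count. Section 7.3 also selects covariates by an absolute standardized difference above 0.1, so a history balanced between arms would not be selected by that rule, and balance is a case in which the bias is substantial.

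**Working it through.** **The plan's own figures.** Tables 4 and 5 reproduce with a two-proportion test (pooled variance under the null, two-sided alpha 0.007, 80,000 vaccinated). For 0.3 per 1,000, VE 90%, ratio 1 vs 0.5:
- pooled proportion = (12 + 2.4)/120,000 = 0.00012
- null SE = 6.71e-5; alternative SE = 8.87e-5
- power = Φ[(0.00027 − 2.697 × 6.71e-5)/8.87e-5] = Φ(1.00) = 0.842, against 0.84 stated.

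All 27 entries agree within 2 points. The power figures are not in question.

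**Inputs**
- I0 = 30 per 1,000 unvaccinated over about 4 months (122 days), Section 9.
- Relevant window: an infection d days before index is d + 14 days old when counting starts, so a 90-day rule matters only for d ≤ 76.
- s = number per 1,000 infected in that window = 30 × 76/122 = 18.7, assuming the plan's rate also held before index. Cross-check from Tables 1 and 2, age 12 and over: 295,395/3,986,331 = 7.4% in 2020. Spread evenly over the 306 days from March to December (assumed), this gives 74.1 × 76/306 = 18.4 per 1,000.
- q = chance of a repeat code or positive on day 14 or later = 10-20%. This is an assumption; the protocol gives no figure.

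**Formula.** Observed VE = 1 − [I0(1 − VE) + s_v q]/[I0 + s_u q], a ratio of cumulative incidences used as an approximation to the HR.

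**First interim analysis, true VE 90%**

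| Recent infection per 1,000 (vaccinated, unvaccinated) | q = 10% | q = 20% |
|---|---|---|
| Equal (18.7, 18.7) | 1 − 4.87/31.87 = 84.7% | 1 − 6.74/33.74 = 80.0% |
| None in the vaccinated (0, 18.7) | 1 − 3/31.87 = 90.6% | 1 − 3/33.74 = 91.1% |

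Setting the observed ratio equal to the true one gives s_v/s_u = 1 − VE as the point of no bias. At VE 90%, the estimate is therefore pulled down unless recent infection in the vaccinated is less than a tenth of that in the unvaccinated. At lower VE an upward shift is easier: at true VE 70% with none in the vaccinated, 1 − 9/31.87 = 71.8% and 1 − 9/33.74 = 73.3%.

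**Sensitivity to the assumptions, equal shares, true VE 90%**
- 1% recently infected, q = 5%: 1 − 3.5/30.5 = 88.5%
- 5% recently infected, q = 20%: 1 − 13/40 = 67.5%. The 5% share is well above the 1.9% that the plan's rate implies.

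**Two years of follow-up**, plan's rate held constant (assumed): I0 = 6 × 30 = 180 per 1,000, carry-over unchanged, equal shares.
- q = 10%: 1 − 19.87/181.87 = 89.1%
- q = 20%: 1 − 21.74/183.74 = 88.2%

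**Objective 8 person-time.** Section 8.4 puts the 90-day condition on the event and otherwise follows the primary analysis, and Section 8.2 divides by total person-years. No later start of risk is stated. Assume 120 days of follow-up and, for those affected, a mean of 38 days in which no event can count (38/120 = 0.317). At true VE 80%:
- 20% affected in each arm: both rates are understated by 0.2 × 0.317 = 6.3%; VE stays at 80%.
- 10% of vaccinated, 30% of unvaccinated: HR = 0.2 × 0.968/0.905 = 0.214; VE 78.6%.
- 30% of vaccinated, 10% of unvaccinated: HR = 0.2 × 0.905/0.968 = 0.187; VE 81.3%.

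**The case against.** The strongest reply has four parts.

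1. **Partial safeguards exist.** The exclusion of outcomes before day 14 removes recently infected people whose repeat record falls in that window, where repeats may be most frequent. Section 8.4 also plans VE by history of COVID-19 at the first interim analysis, and a stratum without history would be free of recorded carry-over. Both points stand as mitigation. The first means q must be read as the chance of a record on day 14 or later. Neither corrects the primary estimate.

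2. **The missing rule may be a drafting gap.** Section 7.2 speaks of incident cases, and Section 8.4 defines incident with the 90-day interval. But that definition is written for Objective 8, and Section 7.2 ties the word to no look-back. A programmer following Section 7.2 would count the events.

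3. **The size rests on an assumed repeat rate and on the shortest follow-up.** This stands. The range is a sensitivity analysis for an early interim look.

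4. **The start of risk time in Objective 8 can be left to the analysis plan.** This largely stands. Section 11 lists a separate statistical analysis plan, which is not shown here and could set it.

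A reader might also infer that both primary outcomes are equally exposed. The documents do not support that: a follow-up code or incidental positive should mostly fail the chart review required for severe disease, although that review is not a reinfection rule. Nor do they support reading Objective 8's VE as seriously distorted, since VE moves only if the recency of infection differs between arms.

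**Conclusion.** The point holds for Primary Objective 1 and for the cohort secondary objectives that use the COVID-19 diagnosis outcome. As written, records of an infection before index can be counted as new events, and Sections 7.2 and 8.4 contradict each other on Objective 8. This is a rule stated wrongly, not detail deferred to a later document.

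At the first interim analysis a true VE of 90% would read about 85-80% with equal recent infection in both arms and a 10-20% repeat rate, or about 91% with no carry-over in the vaccinated. The repeat rate and the split between arms are assumptions, so the direction is not fixed. At the final analysis, with about two years of follow-up, the loss is about 1-2 points in the equal case. It would be too strong to say that the final result is invalid. With power above 99.9% for this objective, though, random error is small, and an early bias of several points would not be obvious from the confidence interval.

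**What to change.** In Section 7.2, count an event in every cohort objective only if it occurs more than 90 days after the most recent prior COVID-19 code or positive molecular test. Start time at risk at the later of day 14 after the index date and day 91 after that prior infection. Use the same start in Objective 8, so that events and person-time match. Remove Objective 8 from the rule-free definition, or cross-refer Section 7.2 to Section 8.4, so that the two agree. State whether a repeat record inside the interval restarts the 90 days.

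The cost is a change of wording and one derived date. About 19 per 1,000 members (2%) are affected. With a late start they lose on average 38 of 122 days, or 0.0187 × 38/122 = 0.6% of four-month person-time; excluding them outright would cost the full 2%. Neither would materially reduce power for Primary Objective 1.
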